### Primary and secondary endpoints

All participants will be followed up regularly according to the schedule shown in Fig. 2 at the stated intervals after surgery for at least 3 years. At the follow-up visits, patients will undergo laboratory tests and abdominal ultrasonography as described in Fig. 2. CT or MRI will be performed in cases of suspected stone recurrence or cholangitis. Laboratory tests mainly include routine blood, liver and kidney function, electrolytes, procalcitonin, C-reaction protein, carcinoembryonic antigen, carbohydrate antigen 199 (CA199) and alpha-fetoprotein (AFP).

The primary efficacy endpoint of the trial will be the incidence of biliary complications (stone recurrence, biliary stricture, cholangitis). Stone recurrence will include any bile duct stones detected with any imaging modality during follow-up. Biliary stricture will be defined as clinically evident stenosis and subclinical stenosis proven by endoscopic examination or reoperation. The diagnosis of cholangitis will be based on clinical evidence (abdominal discomfort/pain, jaundice or fever associated with hepatolithiasis).

The secondary outcomes will be the surgical, perioperative and long-term follow-up outcomes. The surgical outcomes will include operative duration, intraoperative blood loss, intraoperative blood transfusions, stone distribution and SO function. The perioperative events occurring within 90 days after surgery will be recorded, including biliary leakage, wound infection, pulmonary infection, reoperation, hepatic injury, haemorrhage, bowel function recovery, intra-abdominal fluid collection or abscess, mortality, duration of postoperative hospital stay and total hospitalization expenditure. The indices of long-term follow-up outcomes will be hepatic injury, stone recurrence, biliary stricture, rate of unplanned readmission for HL, incidence of cholangitis and quality of life. Postoperative complications will be graded based on severity according to the Clavien-Dindo definition (shown in Additional file 2: Table S1) [8]. Long-term quality of life will be assessed by clinical grading according to Terblanche et al. [9]. Grades I and II constituted excellent or good results, grade III fair and grade IV poor (shown in Additional file 2: Table S2).

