### Randomization and blinding

To achieve comparable groups of known and unknown risk factors, randomization will be performed. Patients meeting the eligibility criteria will be randomly assigned (1:1) to the T-tube drainage arm or Roux-en-Y HJ arm by computer-generated allocation based on the envelope method and the hierarchical block randomization method. The envelopes will be opened after common bile duct exploration.

Blinding of the surgeons and patients is not feasible due to the obviously different characteristics of the two types of biliary drainage. However, the statisticians will be blinded to the treatment allocation during data collection and analysis.

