### Standardization of perioperative care

The operations will be performed by two senior surgeons ([name] and [name]) who are equally skilled in T-tube drainage and Roux-en-Y HJ. Intraoperative flexible choledochoscopy (CHF-P20, external diameter, 4.9 mm; Olympus, Tokyo, Japan) will be routinely performed to explore the biliary ducts, identify the function of the SO and remove residual stones. All patients included in the study should successfully undergo cleaning of all ductal stones, removal of all strictures and elimination of the non-functioning liver segments that harbour bacteria and serve as foci of infection. For the patients with T-tubes, cholangiography will be performed to ensure that all the stones are clean before the T-tubes are removed. If there are residual stones, they could be cleaned through postoperative choledochoscopy. Indications for liver lobe resection will include a liver segment or lobe filled with stones that were inaccessible by other approaches for treatment, strictures associated with stones, atrophy of the affected liver segments or lobe, presence of liver abscess, or suspected cholangiocarcinoma. The selection criteria for hepatectomy will require patients to have Child’s A grade liver function and no evidence of portal hypertension. The grading criteria for SO function are as follows: normal—the shape of the SO is circular (Fig. 3a) or comma-like (Fig. 3b) with normal rhythmic contractions, a flexible choledochoscope cannot enter the duodenum and the SO can completely close without gaps during closure; SOL (shown in Additional file 3: Video S1-Grading criteria for the SO function laxity)—the shape of the SO is oval (Fig. 3c) or irregular (Fig. 3d), a flexible choledochoscope can enter the duodenum with some resistance, the SO cannot completely close during closure or reflux of food or methylene blue can be seen in the common bile duct during flexible choledochoscopy; and loss of function—the flexible choledochoscope can directly enter the duodenum, and no contractions are observed after the morphine-neostigmine test.

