### Statistical analysis

The two-sided null hypothesis for the primary outcome measure states that both study interventions lead to a similar rate of stone recurrence; the alternative hypothesis is that one intervention will perform better than the other. The continuous variables will be recorded as the mean ± SD (for normally distributed variables) or medians and interquartile ranges (for skewed parameters) and will be statistically analysed with Student’s *t* test and the non-parametric Mann-Whitney *U* test, respectively.

Categorical data will be presented as frequencies and group percentages and compared with Fisher’s exact test. Graded data, including age, quality of life and Clavien-Dindo classification, will be compared with the Wilcoxon signed-rank test.

The odds ratio for having biliary complications will be determined with a logistic regression model. The homogeneity of the two groups will be described by comparing the demographic data and the baseline values.

All analyses will be performed on an intention-to-treat (ITT) basis. Statistical Package for the Social Sciences (SPSS) 10.0 (SPSS Inc., Chicago, IL, USA) will be used for statistical analysis. Statistical significance will be defined as *P* < 0.05.

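### Stone distribution and sphincter of Oddi function are listed as surgical outcomes, although both are settled before the envelope is opened and neither can show a treatment effect

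*Protocol article*

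**What the plan says.** Under *Primary and secondary endpoints* the protocol article states: "The secondary outcomes will be the surgical, perioperative and long-term follow-up outcomes". It then defines the first of these groups as the length of the operation, the blood lost, and "intraoperative blood transfusions, stone distribution and SO function". Stone distribution and sphincter function are therefore two of five named surgical outcomes, and by that route secondary outcomes of the trial.

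Three other sections fix the timing:

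- *Randomization and blinding* has only patients who already meet the eligibility criteria randomised, and adds: "The envelopes will be opened after common bile duct exploration".
- *Standardization of perioperative care* says that intraoperative choledochoscopy "will be routinely performed to explore the biliary ducts, identify the function of the SO and remove residual stones". It gives a three-level scale: normal, laxity, loss of function.
- *Eligibility criteria* require laxity found at operation and stones extracted without residue. They exclude a normal sphincter, complete loss of function, and residual stones.

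*Statistical analysis* compares categorical data with Fisher's exact test at the 0.05 level and makes no exception for these two variables. It also plans a baseline comparison: "The homogeneity of the two groups will be described by comparing the demographic data and the baseline values". The odds ratio for biliary complications is to come from a logistic regression whose covariates are not listed.

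**The concern.** An outcome has to be something that the allocated treatment could change. A variable that is fixed before allocation cannot be changed by it, so comparing it between arms does not answer a treatment question.

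The stake is mainly one of reading. If stone distribution differed between arms and was reported as a secondary outcome, it could be taken for a consequence of the drainage method. Its useful meaning would be missed: an imbalance in a pre-allocation variable is either chance or a warning about how patients were allocated. That warning has some value here, because the surgeons are not blinded and the envelopes are opened during the operation. Sphincter function as an outcome would simply give an empty comparison.

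**Working it through.** The article gives no figure for this point, so the main check sets its sections side by side. A short power calculation follows for the optional part of the fix.

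**1. Sphincter function**
- Graded at: the choledochoscopy that forms the duct exploration.
- Envelope opened: after that exploration.
- Grades on the scale: 3. Grades excluded by eligibility: 2 (normal, complete loss). Grades left: 3 − 2 = 1.
- Result: one value in both arms, so there is nothing to compare. A finer description within laxity, such as oval against irregular shape, could vary, but it too is seen before allocation.

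Could a postoperative measurement be meant? In the hepaticojejunostomy arm the duct is divided and its duodenal side closed. The only postoperative choledochoscopy mentioned is for T-tube patients with residual stones. No follow-up measurement comparable across the arms is described.

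**2. Stone distribution**
- It describes where the stones lay in the disease as found at operation.
- Complete extraction is an entry condition, and only eligible patients are randomised.
- It cannot stand for later stones, because stone recurrence is listed separately among the long-term outcomes.
- Result: a pre-allocation variable. Under sound randomisation the null hypothesis of no difference is true by design, so a test at 0.05 rejects with probability at most 5%, and every such rejection is chance. A departure beyond chance would point to allocation, not to treatment.

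**3. Stone distribution as a covariate (illustration)**

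Inputs from the article: 30% v 15% with biliary complications, 210 patients enrolled, 10% withdrawal, two-sided 0.05.
- Evaluable patients: 210 × 0.9 = 189; 189 / 2 = 94.5, taken as 94 per arm.

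Inputs that are assumptions and not in the article: stone distribution has two levels split 50:50, with an odds ratio of 2 to 4 for biliary complications. The overall rates are held at 30% and 15%.

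Method: likelihood-ratio test of treatment in logistic regression, without and with the covariate.
- Unadjusted power, computed exactly at 94 per arm: 70.3%. With the overall rates held fixed and the covariate drawn at random, this does not depend on the covariate's odds ratio.
- Adjusted power, simulated at 94 per arm (4,000 runs): 72.2% (odds ratio 2), 72.6% (3), 72.6% (4).
- Adjusted power, simulated at 93 per arm (3,000 runs): 71.4% (odds ratio 2), 72.9% (4).
- Simulation standard error at 4,000 runs: √(0.7 × 0.3 / 4000) = 0.0072, about 0.7 points.

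Reading the runs together, power goes from about 70% to about 71–73%, a gain of roughly one to three points. That the starting value lies below the 80% planned under *Number of patients needed* is a separate sample-size matter, which this point neither causes nor repairs.

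**The case against.** The strongest reply is that little depends on this. The list may be no more than a loose catalogue of operative findings to be recorded, and nobody is likely to claim benefit for a drainage method from where stones lay before it was chosen. The 5% is only the nominal level that any true-null secondary comparison carries. Relabelling alone would also not remove a test, since baseline values are to be compared between arms in any case.

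Most of this stands as a limit on importance. It does not remove the misclassification: the text positively assigns both variables to the secondary outcomes, and an unseen analysis plan that adds covariates would not change that. The remark about relabelling is right, and the fix therefore has to say that the description is without a test.

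A reader might go further and infer that the plan has thrown away a usable covariate and so lost power. The article does not support that:

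- It neither names nor bars covariates in the logistic model, and it does not name the strata of its block randomisation. Those choices are commonly left to the full protocol or the analysis plan, which are not shown.
- Stone distribution is still recorded, and being listed as an outcome does not keep it out of a model.
- Sphincter function, constant on the protocol's scale, could not serve as a covariate at all.
- The power gain is small and rests on an assumed prevalence and odds ratio.

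**Conclusion.** The point holds as a misclassification of two pre-randomisation variables. Two of the five surgical outcomes cannot answer a treatment question: sphincter function because eligibility leaves one grade, and stone distribution because it precedes allocation. This follows from the article's own sections and needs no outside assumption.

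It is minor. The primary endpoint, its analysis and the sample size are untouched. Adjusting for stone distribution is an improvement worth offering, not the correction of an error. Its size, one to three points of power, depends entirely on the assumed two-level 50:50 split and odds ratio of 2 to 4.

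**What to change.** 1. Under *Primary and secondary endpoints*, delete stone distribution and sphincter function from the surgical outcomes.
2. List both as pre-randomisation (baseline) characteristics found at operation. State that they are described by arm, without a test for treatment effect. For sphincter function, note that all eligible patients are graded as lax; any finer description within laxity belongs in the same table.
3. As an improvement, pre-specify stone distribution, with its levels defined in advance (for example unilateral or bilateral), as a covariate in the logistic model for biliary complications. Do not enter sphincter function. The adjusted odds ratio is conditional on the covariate, so say which estimate is primary.

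The cost is a change of wording and one model term. No new data are needed, since both variables are already to be recorded.

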### Number of patients needed

The sample size is based on a two-sided *t* test for differences with respect to the primary parameter and the primary analysis. In a retrospective analysis of our own series, the incidence of biliary complications was 30% in patients with HL with SOL undergoing T-tube drainage. The calculated sample size was 186 (93 per group), with 80% statistical power to detect a difference in the supposed incidence of biliary complications of 15% (30% in the T-tube drainage group versus 15% in the Roux-en-Y HJ group). Given an estimated withdrawal rate of 10%, the minimum required sample size would be 204 patients. We plan to enrol a total of 210 patients (105 per group).

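### Long-term quality of life is measured only by a four-level clinical grade of the surgical result, which as described is poorly suited to support a quality-of-life conclusion

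*Protocol article*

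**What the plan says.** In the Protocol article, Primary and secondary endpoints, the list of long-term secondary outcomes ends with "rate of unplanned readmission for HL, incidence of cholangitis and quality of life". The same section names the measure: "Long-term quality of life will be assessed by clinical grading according to Terblanche et al". It then says how the levels are read: "Grades I and II constituted excellent or good results, grade III fair and grade IV poor". For the definitions of the grades it points to Additional file 2, Table S2, which is not among the documents at hand.

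Under Statistical analysis the grade is handled as ordered data and keeps the name quality of life: "Graded data, including age, quality of life and Clavien-Dindo classification, will be compared with the Wilcoxon signed-rank test".

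On blinding, the section Randomization and blinding says: "Blinding of the surgeons and patients is not feasible due to the obviously different characteristics of the two types of biliary drainage". It adds that "the statisticians will be blinded to the treatment allocation during data collection and analysis". No blinded outcome assessor is described, and the article does not say who assigns the quality-of-life grade.

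**The concern.** Quality of life is normally understood as the patient's own account of function and wellbeing. The measure chosen is called a clinical grading, and its levels describe results. Both terms point to a rating of the outcome of surgery. Because the article names the instrument, cites its source and explains its levels, this is a choice that has been made. It is not a detail left to a fuller document.

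What is at stake is interpretation. The Discussion says the trial should lead to a recommendation of the better surgical method for these patients. If the grade differs between arms, the difference could be reported as a gain in quality of life when it may partly restate the biliary complications already counted in the primary endpoint. If the grade does not differ, the arms could be described as equal in quality of life on the strength of a scale that may not register differences among patients free of biliary complications.

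**Working it through.** The article states no figure for quality of life: no expected distribution, no target difference and no power. The sample size rests on the primary endpoint alone, so there is no planned figure to reproduce. The check is mainly a reading of the text.

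**1. Name against measure.**
- Outcome name, in both Primary and secondary endpoints and Statistical analysis: quality of life.
- Measure: one clinical grading with four levels.
- What the levels describe: results, with levels I and II described together.
- Patient-completed instrument: none named in any section.

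The name claims more than the description of the measure delivers.

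**2. Possible overlap with the primary endpoint.** The primary endpoint combines stone recurrence, biliary stricture and cholangitis, and cholangitis is diagnosed from symptoms and signs such as pain, jaundice or fever. A clinical grade of the result of biliary surgery could plausibly draw on the same information. How far it would do so can be written down, but not fixed.

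Inputs from Number of patients needed: biliary complications in 30% of T-tube patients and 15% of hepaticojejunostomy patients. So 100% − 30% = 70% and 100% − 15% = 85% are free of complications.

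Let *a* be the share of complication-free patients graded I or II, and *b* the share of patients with a complication graded I or II. Assume both are the same in the two arms, so that the grade carries nothing beyond event status. Then:

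- T-tube arm, grades I–II: 0.70*a* + 0.30*b*
- Hepaticojejunostomy arm, grades I–II: 0.85*a* + 0.15*b*
- Difference: 0.15*a* − 0.15*b* = 0.15(*a* − *b*)

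The documents give neither *a* nor *b*. Over the possible range:

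| Assumed *a* − *b* | Difference in grades I–II due to event status alone |
|---|---|
| 1 (grade follows event status exactly) | 0.15 × 1 = 15 points, the whole primary difference |
| 0.5 | 0.15 × 0.5 = 7.5 points |
| 0 (grade unrelated to event status) | 0 points |

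The overlap could be anything from none to complete. Table S2 would narrow this range; the article does not.

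**3. Does the analysis collapse the scale?** Levels I and II are described together, but the Statistical analysis section treats quality of life as graded data for a rank-based comparison. The text therefore does not say that I and II are pooled. If they are kept apart, the split between them could still distinguish patients who had no complication.

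**4. Blinding.** Surgeons and patients know the procedure; the statisticians do not. The rater is not named. A patient questionnaire would also be completed unblinded. Lack of blinding is thus an added risk of bias under either measure and does not favour one over the other.

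**The case against.** The strongest reply is that the choice is disclosed. The article says openly that a clinical grading is used, cites it and points to a definition table. Those definitions are not shown, so any statement about what the grades contain is conjecture; if they are built on patients' symptoms, the gap between name and measure is narrower. Only one secondary outcome is involved, and how the authors will report it is not known.

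Much of this stands, and it rules out several stronger readings that a reader might infer:

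- *That the measure is an unblinded clinician's opinion.* The rater is not stated, and a condensed article may leave that to the full protocol. It is a likely inference from the wording, no more.
- *That the grade cannot support any quality-of-life statement, or mostly repeats the primary endpoint.* Both depend on Table S2. The arithmetic shows that overlap is possible; it does not establish it.
- *That the measure fails because it misses the burden of the external tube.* The outcome is defined as long-term, so early tube burden lies largely outside it. The article gives no duration for the tube and does not mention digestive change after reconstruction. Some early burden is covered by the 90-day outcomes, such as bowel function recovery and hospital stay.

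What the reply does not do is restore the match between name and measure. Disclosing that a clinical grade is used does not make it a measure of quality of life, and the analysis section carries the label forward without qualification.

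**Conclusion.** The point holds as a mismatch between label and measure. The only instrument given for long-term quality of life is a coarse four-level clinical grade of results, with no patient-reported measure beside it. As described, it is poorly suited to support a conclusion about quality of life. Overlap with the primary endpoint is plausible, but its extent is unknown: between 0 and 15 percentage points at the design rates, under the assumption that the grade reflects event status only.

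This rests on Table S2 following the clinical wording of the article. The importance is low: one secondary outcome and the wording of its conclusion are affected, while the primary endpoint, its analysis and the sample size are not.

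**What to change.** In Primary and secondary endpoints and in Statistical analysis, rename the outcome *long-term clinical result grade*. Analyse it on all four ordered grades, without merging I and II, using a method for two independent groups (the signed-rank test named there is for paired data, which is a separate matter). Draw no quality-of-life conclusion from it. State who assigns the grade, if the full protocol does not already do so. This costs wording only; the downside is that the trial gives up its quality-of-life claim.

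Optionally, if quality of life is to remain an outcome, add a short validated patient-completed questionnaire at the existing visits (3 and 6 months, 1, 2 and 3 years) and keep the grade as a separate clinical outcome. The cost is a few minutes per visit, plus three limits to accept: patients are unblinded; enrolment began in February 2020, so those already enrolled will have no preoperative baseline; and some of them may lack the early assessments.

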### Randomization and blinding

To achieve comparable groups of known and unknown risk factors, randomization will be performed. Patients meeting the eligibility criteria will be randomly assigned (1:1) to the T-tube drainage arm or Roux-en-Y HJ arm by computer-generated allocation based on the envelope method and the hierarchical block randomization method. The envelopes will be opened after common bile duct exploration.

Blinding of the surgeons and patients is not feasible due to the obviously different characteristics of the two types of biliary drainage. However, the statisticians will be blinded to the treatment allocation during data collection and analysis.

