### Eligibility criteria

#### Inclusion criteria

The following are the inclusion criteria:
Aged between 18 and 70 yearsDiagnosed with HL with SOL during the operationUnderwent foci removal, stone extraction without residue and stricture correction during the operationProvided written informed consentWas willing to complete a 3-year follow-up.

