### Trial interventions

All patients with SOL underwent common bile duct exploration and complete stone extraction. The surgical procedures of the T-tube drainage arm and Roux-en-Y HJ arm are as follows.

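### Envelope opening is tied to bile duct exploration, not to confirmation of all operative eligibility criteria, so an unblinded surgeon could settle some of them knowing the arm

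*Protocol article*

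**What the plan says.** The protocol article, Randomization and blinding, states who is allocated: "Patients meeting the eligibility criteria will be randomly assigned (1:1) to the T-tube drainage arm or Roux-en-Y HJ arm". It then states when: "The envelopes will be opened after common bile duct exploration". The same section accepts that "Blinding of the surgeons and patients is not feasible".

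Several eligibility criteria are results of the operation. Inclusion criteria requires that the patient underwent "foci removal, stone extraction without residue and stricture correction during the" operation, and Exclusion criteria lists a stone left at operation. Standardization of perioperative care repeats the requirement: "All patients included in the study should successfully undergo cleaning of all ductal stones, removal of all strictures and elimination of the non-functioning liver segments".

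Trial interventions describes what both arms have in common before it turns to the two drainage procedures: "All patients with SOL underwent common bile duct exploration and complete stone extraction". Resection of diseased segments and stricture correction are not named there.

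Statistical analysis places all analyses on an intention-to-treat basis.

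**The concern.** Allocation should be revealed only when nothing about eligibility is left to judge. Here the trigger is one surgical step, while eligibility depends on several, and not all of them are stated to be finished by then. If a criterion is still open when the envelope is opened, an unblinded surgeon settles it with the arm known.

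A patient who then fails the criterion goes one of two ways. If the patient is removed, the exclusion comes after randomisation and may depend on the arm. If the patient is kept, an ineligible patient is in the comparison. The criteria at issue are prognostic: Background and Discussion name bile duct stricture and residual stones as risk factors for recurrence, and stone recurrence and biliary stricture are components of the primary endpoint. Unequal exclusion would therefore act directly on that endpoint.

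**Working it through.** The plan gives no figure on this point to reproduce. The check is a reading of the order of steps, one operative criterion at a time, against the stated trigger.

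1. **Sphincter laxity.** Graded at the routine intraoperative choledochoscopy, which also explores the ducts (Standardization of perioperative care). Known at the trigger.
2. **No residual stone.** Trial interventions names complete extraction alongside exploration and ahead of the arm procedures, and the same choledochoscopy serves to remove residual stones. Clearance is most naturally read as done by the trigger. One gap remains: an indication for liver resection is a segment or lobe full of stones that other approaches cannot reach. In those patients clearance depends on the resection as well as on exploration.
3. **Removal of foci.** Required by Inclusion criteria and by Standardization of perioperative care. No section places it before the envelope.
4. **Stricture correction.** Required in the same two places. No section places it before the envelope.

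So at the stated trigger the first criterion is settled, the second probably is, and the third and fourth are not placed in time at all.

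**Can the size be estimated?** Inputs from the plan (Number of patients needed): 105 per arm, with planning rates of 30% (T-tube) and 15% (Roux-en-Y hepaticojejunostomy, HJ). Two inputs have to be assumed: k patients removed after opening, each with event risk r. The arm's rate p becomes

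(p × 105 − k × r) / (105 − k)

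- HJ arm only, k = 3, r = 0.5: (15.75 − 1.5)/102 = 14.0%; difference 30 − 14.0 = 16.0 points.
- HJ arm only, k = 10, r = 0.8: (15.75 − 8)/95 = 8.2%; difference 30 − 8.2 = 21.8 points.
- T-tube arm only, k = 3, r = 0.5: (31.5 − 1.5)/102 = 29.4%; difference 29.4 − 15 = 14.4 points.
- T-tube arm only, k = 10, r = 0.8: (31.5 − 8)/95 = 24.7%; difference 24.7 − 15 = 9.7 points.
- Both arms, k = 10, r = 0.8: 24.74 − 8.16 = 16.6 points.

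Against the planned 15 points, the result can rise, fall or hardly move, depending on k, r and the arm affected. The document gives none of these three. The base is also doubtful: the planning rates are meant for a trial population that by its own criteria has no residual stone, while the formula treats them as already including patients who fail a criterion. If those patients were never part of that population, the HJ rate stays at 15%. These lines show only that no estimate is available.

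**The case against.** The strongest reply is that the article already gives the right order. Randomization and blinding limits allocation to patients who meet the criteria, the Abstract says the same and lists the operative criteria among them, and Inclusion criteria words them as completed acts. Opening after exploration can be read as an earliest time, which is compatible with waiting until everything else is done. This stands as evidence of intent. It does not make the trigger sufficient: a surgeon who opened the envelope straight after exploration, with a resection still to come, would be following the timing sentence as written.

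The pairing of stone extraction with exploration in Trial interventions also stands, and it narrows the point. A reader might infer that surgeons do judge residual stones after learning the arm. No section says so, and this pairing points the other way.

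A reader might also take the T-tube provision, "If there are residual stones, they could be cleaned through postoperative choledochoscopy", as a sign of unequal eligibility decisions. That step is postoperative, while the exclusion concerns a stone left at operation. It is part of the T-tube care described and does not show that eligibility is judged differently by arm.

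Intention-to-treat would keep allocated patients in the analysis, and no section provides for removing a patient found ineligible after allocation; Withdrawal deals with patients who leave at their own request. Removal is therefore a possibility and not a stated plan. Intention-to-treat does not, however, prevent ineligible inclusions.

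Finally, the flowchart and the schedule are not shown and a full protocol exists. Either may set out the order. Recording details may properly sit there, so their absence from the article is not the point. The point is that the trigger the article does state falls short of its own criteria.

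**Conclusion.** The concern holds in a limited form. The stated trigger is badly fixed: it is not tied to completion of all the operative criteria, most clearly removal of foci and stricture correction, and less so stone clearance. With unblinded surgeons this leaves room for arm-dependent exclusion or for ineligible inclusions. The text is ambiguous on order and does not establish that eligibility is decided after allocation.

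The size and direction of any bias cannot be estimated from the document. A reader might infer an artefact of 1 to 7 points from the HJ-only calculation (15% falling to between 14.0% and 8.2%). That range rests wholly on assumed one-arm removals and assumed event risks, and should not be quoted as an estimate.

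The conclusion assumes that the timing sentence is the operative instruction to the surgeons and that no unseen document sets a stricter one. It is worth correcting because the safeguard is simple and the stated rule does not provide it.

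**What to change.** Reword the timing sentence in Randomization and blinding along these lines: the envelope is opened only after all operative eligibility criteria (removal of foci, stricture correction, stone clearance, sphincter laxity) have been met and recorded on the case report form, and immediately before the arm-specific drainage step. Add that every patient whose envelope is opened stays in the intention-to-treat analysis and is not removed for an eligibility reason.

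The record relies on the choledochoscopy that is already routine, so no procedure is added, and the surgical content of either arm is unchanged. No sample-size figure changes. The cost is a short amendment to the protocol text and one line on the form. Trial status gives a start of enrolment in February 2020 and an expected end around December 2026, so an amendment can protect only patients enrolled after it.
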